### Randomisation

Randomisation takes place at 'condition round' level. The inclusion period is divided into condition rounds using a Latin Square design. Every round takes 5 months and switches when a total of n = 75 is reached. The ranking order of conditions (1–5) is varied to correct for learning effect by the risk counsellors. Each condition is given according to the design shown in Table 2. The control group (condition 6) is constructed in addition to each condition round.

**Table 2 T2:** Latin square design of condition rounds over time at the three clinical genetic centres

	**Conditions**^a^				
	months 1–5	months 6–10	months 11–15	months 16–20	months 21–25

Centre A	1	2	3	4	5
Centre B	2	3	4	5	1
Centre C	5	1	2	3	4

^a^. 1) lifetime risk in numerical format (natural frequencies); 2) lifetime risk in both numerical format and graphical format (population figures); 3) lifetime risk and age-related risk in numerical format; 4) lifetime risk and age-related risk in both numerical format and graphical format; 5) lifetime risk in percentages. Condition 6 (control group) is constructed in addition to each condition round.

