**Figure 1 F1:**
[figure not shown]
Time planning of the intervention and questionnaires in the intervention group (conditions 1–5) and control group (condition 6).

During the additional consultation, risks are communicated in one of five ways (conditions), namely:

1) lifetime breast cancer risk in numerical format (in natural frequencies, i.e. X out of 100),

2) lifetime breast cancer risk in both numerical format and graphical format (i.e. population figures in 10 rows of 10),

3) lifetime breast cancer risk and age-related breast cancer risk in numerical format,

4) lifetime breast cancer risk and age-related breast cancer risk in both numerical format and graphical format, and

5) lifetime breast cancer risk in percentages.

Since the information given during the intervention not only differs from usual care regarding the format of the risks but also to the extent to which the information is structured, two control conditions are included. Condition 5, in which the risk is communicated in percentages as in the standard genetic counselling session (usual care), controls for the effect of giving risk information also in a structured way, enabling us to compare the effects of different risk formats. Condition 6, in which no intervention is given (usual care, henceforth defined as the control group) is used to control for the effect of repetition of the risk information (as compared to condition 5), and will control for Hawthorne effects [38].

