### Study population

Women with a family history of breast cancer who are first-time attendees applying for breast cancer counselling are invited to participate in the study. A family history of breast cancer is defined as having or having had at least one first-degree- and/or paternal second-degree family member with breast cancer. Women are considered ineligible if they are under 18 years of age, have evident psychiatric illness or terminal disease, and are unable to read and write Dutch. Women with a personal history of breast or ovarian cancer are also excluded, because of the complexities in risk counselling of women with a previous history of cancer. Participants are allocated into an intervention or control group (for randomisation procedure, see below). Stratification to first-degree family members is applied to ensure that all family members receive the same condition.

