### Procedure

Women applying for genetic breast cancer counselling are invited to participate by means of an information letter send to their home address. All participants provide written informed consent. In the intervention group, participants receive a self-administered questionnaire at four points in time (T0, T1, T2, T3), the control group receives this at three points in time (T0, T1C, T2C) (see Figure 1):

- T0 (baseline): The women will receive the first questionnaire at home before their first appointment with the genetic counsellor.

- T1 (after standard counselling session): A second questionnaire will be given after the standard genetic counselling session with the genetic counsellor and prior to the intervention (additional counselling with the risk counsellor).

- T2/T1C (2 weeks follow-up): A third questionnaire will be sent to the woman's home address at 2 weeks after the intervention, or a comparable point in time (control group).

- T3/T2C (6 months follow-up): The final questionnaire will be sent to the woman's home address.

A maximum of two reminders is sent to participants not returning their questionnaires. The three risk counsellors (one for each clinical genetics centre) who provide the intervention, have been specifically trained for this study. The intervention lasts for approximately 30 minutes. The risk counsellor is informed about the content of the previous standard counselling session by means of a "checklist after standard counselling", which the genetic counsellor fills in immediately after each session. This checklist includes information about the participant's risks e.g. individual estimated risk of getting breast cancer, also describing the risks formats that were used during counselling. When risks are not yet known, because, for instance, medical records need to be checked, intervention takes place after a second visit. Thus, enforcement of an intervention implies that in the genetic counselling session with the genetic counsellor at least the woman's breast cancer risk group (e.g. low, moderate, high) was communicated.

After the intervention, all participants receive a BRISC brochure in which risks are presented corresponding to the format of the intervention given.

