Two control conditions are introduced in the BRISC study: condition 5 in which the risk information is communicated in percentages as is commonly done in usual care, and a second control condition (condition 6) in which no intervention is given. With these two control conditions, it is possible to distinguish between the effect of repetition and the effect of giving the risks in a structured way on the one hand, and between the effects of giving the risks in a structured way in different formats on the other.

Because the genetic counsellor involved has no role in the inclusion of participants, selection bias is restricted, other than from self-selection. Cluster-randomisation is applied as it is too complex to randomise at the level of counsellees because in that case a risk counsellor is asked to give different risk formats of genetic risks to different counselees on the same day. An exception is made for participants who are close family members.

The risk counsellors who give the intervention are not involved in usual care. This will overcome concerns of contamination bias. All risk counsellors are women, eliminating bias due to gender differences. The Latin Square design and the control group, which is constructed in addition to all condition rounds, both serve to eliminate bias due to time. To achieve uniform risk communication in the genetic counselling sessions, several precautions have been taken (e.g. striving for a standard counselling procedure, "counselling checklist", "checklist after standard counselling"), minimising confounding.

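### No random allocation to the usual-care control (condition 6) is described, and the only stated randomisation unit cannot produce one

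*Protocol article*

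**What the plan says.** All references are to the protocol article.

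- **Study population** points forward to a procedure covering intervention versus control: "Participants are allocated into an intervention or control group (for randomisation procedure, see below".
- **Randomisation** names one unit: "Randomisation takes place at 'condition round' level". The ordering concerns the five active conditions only: "The ranking order of conditions (1–5) is varied to correct for learning effect by the risk counsellors". Table 2 fills its 15 centre-by-period cells with conditions 1–5. On usual care, the text and the table footnote say only: "The control group (condition 6) is constructed in addition to each condition round".
- **Intervention** defines the arm in question: "Condition 6, in which no intervention is given (usual care, henceforth defined as the control group".
- **Discussion** explains why counsellees are not randomised individually: "in that case a risk counsellor is asked to give different risk formats of genetic risks to different counselees on the same day". It also offers a safeguard: "Because the genetic counsellor involved has no role in the inclusion of participants, selection bias is restricted, other than from self-selection". It credits the concurrent control group with dealing with bias due to time.
- **Sample size and power** bases the calculation on a difference between the intervention group and the control group: 60 women per condition, 360 in total, 450 after 20% drop-out.

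**The concern.** A reader who follows the cross-reference finds a procedure that settles which format a centre gives in which period. It does not settle who, among the women consenting in that centre and period, gets no additional consultation. The one argument against individual randomisation does not cover that choice either.

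Two things depend on condition 6. One is the intervention-versus-control comparison on which the trial is powered. The other is condition 5 versus condition 6, which is meant to isolate the effect of repeating the risk information. If women who become controls differ from the others in a way related to risk perception, the difference would be read as an effect of the intervention. It would also enter every contrast with condition 6 in the same direction, so agreement among the five contrasts would give no reassurance.

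**Working it through.** **1. Can the stated unit allocate condition 6?** The unit is the condition round. Table 2 gives 3 centres × 5 periods = 15 centre-rounds, each carrying one of conditions 1–5, and each of those conditions appears three times. Condition 6 is present alongside all 15. Randomising rounds can assign one format to a centre-round. It cannot divide the women inside a centre-round between that format and usual care. A second, within-round step is needed, and none is described.

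**2. Does the stated obstacle apply to that step?** The obstacle is that a risk counsellor would have to give several formats in one day. Condition 6 has no session with a risk counsellor. Allocating women to this round's format or to no extra consultation leaves exactly one format in use in each centre-round, so the obstacle does not arise.

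**3. Do the stated safeguards reach it?** The genetic counsellor's lack of a role concerns inclusion in the study. It does not say who or what decides between the two groups after inclusion. Concurrent controls deal with calendar time and centre, not with differences between women in the same round.

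**4. The plan's own figures.**
- 6 conditions × 60 = 360, and 360 / (1 − 0.20) = 450. The stated total reproduces, at 60 / 0.80 = 75 per condition.
- Reading the round size of 75 as intervention women, 5 rounds × 75 = 375, leaving 450 − 375 = 75 controls.
- Per centre-round: 75 / 3 = 25 intervention women and 75 / 15 = 5 controls, a ratio of 5:1.
- 15 × (25 + 5) = 450. Randomising 5:1 within each centre-round therefore keeps the stated total.

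**5. How much could it matter?** The document gives no figure for imbalance between controls and others, so what follows is an illustration on assumed inputs.
- Assume an imbalance of 0.2–0.3 SD in a factor correlated 0.3–0.5 with the outcome. Bias = imbalance × correlation: 0.2 × 0.3 = 0.06 SD to 0.3 × 0.5 = 0.15 SD.
- For comparison, the difference detectable with 60 per arm (80% power, two-sided 5%) is (1.960 + 0.842) × √(2/60) = 0.51 SD. The assumed bias is about 12–29% of that.
- False-positive rate under bias b: 1 − Φ(1.96 − b/SE) + Φ(−1.96 − b/SE).

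| Contrast | SE (SD units) | b = 0.06 | b = 0.15 |
|---|---|---|---|
| One format vs control (60 vs 60) | √(1/60 + 1/60) = 0.183 | about 6% | about 13% |
| All intervention arms vs control (300 vs 60) | √(1/300 + 1/60) = 0.141 | about 7% | about 19% |

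**The case against.** The strongest reply is that this is an article condensing a full protocol that is not shown. It nowhere says that controls are not randomised, and the cross-reference under Study population suggests that a procedure exists. That stands as far as it goes: a reader might infer that the control group is non-randomised, and the text does not establish this. It does not dispose of the point, because the article does more than omit a detail. It names a procedure for intervention versus control, and the procedure it then gives cannot deliver that allocation.

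Three further replies have weight.

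- **Existing protection.** Controls are concurrent in every centre and round, the genetic counsellor has no part in inclusion, invitation is by letter, and Statistical analyses plans pre–post comparisons with personal variables as covariates. These limit selection bias, but adjustment covers measured differences only.
- **Different filtering of the groups.** Procedure states that "enforcement of an intervention implies that in the genetic counselling session with the genetic counsellor at least the woman's breast cancer risk group" was communicated, with the intervention held over to a second visit if the risk is not yet known. No matching condition is written for controls. A reader might infer that some controls are assessed before being told their risk group. The document does not support that as a fact: Usual care standardises presenting risk as one of three groups, without limiting this to intervention women, and Procedure places the control questionnaire at a time meant to match. What remains is that the matching time is not defined.
- **Ranking of the comparisons.** A reader might infer that contrasts with condition 6 are the weakest in the trial. That is not shown. Conditions 1–5 are compared across only three centre-rounds each, whereas condition 6 is concurrent with all of them.

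**Conclusion.** The point holds in this form: no random allocation of condition 6 is described, the only stated randomisation unit cannot produce it, and the reason given against individual randomisation does not apply to it. The contrasts exposed are those with condition 6, namely the powered comparison and 5 versus 6. Comparisons among conditions 1–5, which can answer research questions 1–3, are not touched by this point.

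The conclusion about the design needs no numerical assumption. The size does: 0.06–0.15 SD, with error rates of about 6–13% (60 vs 60) or 7–19% (300 vs 60), rests on an assumed imbalance and correlation that have no source in the document. It shows what moderate selection would do and is not an estimate of bias in this trial. No figure stated in the plan is shown to be wrong.

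**What to change.** **Allocation.** State how condition 6 is allocated. Preferably, within each centre-round, randomise consenting women 5:1 by a concealed list to that round's condition or to condition 6. Where close relatives take part, randomise the family as one unit, so that the rule giving relatives the same condition is kept. Hold the list away from the genetic and risk counsellors, since the article concedes that genetic counsellors cannot be fully blinded.

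**Timing.** Define the matching time for controls: anchor T1C and T2C to the visit at which the checklist after standard counselling shows that the risk group was communicated, as for the intervention group.

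**If controls have already been enrolled without randomisation.** Report every contrast with condition 6 as non-randomised, adjusted for the T0 value, centre, round and risk group, and say that unmeasured differences remain possible.

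**Cost.** Running a concealed list and making sure the checklist is completed for controls. The total stays at 15 × 30 = 450, each centre-round still uses one format, and the planned number of risk consultations does not change.

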### Procedure

Women applying for genetic breast cancer counselling are invited to participate by means of an information letter send to their home address. All participants provide written informed consent. In the intervention group, participants receive a self-administered questionnaire at four points in time (T0, T1, T2, T3), the control group receives this at three points in time (T0, T1C, T2C) (see Figure 1):

- T0 (baseline): The women will receive the first questionnaire at home before their first appointment with the genetic counsellor.

- T1 (after standard counselling session): A second questionnaire will be given after the standard genetic counselling session with the genetic counsellor and prior to the intervention (additional counselling with the risk counsellor).

- T2/T1C (2 weeks follow-up): A third questionnaire will be sent to the woman's home address at 2 weeks after the intervention, or a comparable point in time (control group).

- T3/T2C (6 months follow-up): The final questionnaire will be sent to the woman's home address.

A maximum of two reminders is sent to participants not returning their questionnaires. The three risk counsellors (one for each clinical genetics centre) who provide the intervention, have been specifically trained for this study. The intervention lasts for approximately 30 minutes. The risk counsellor is informed about the content of the previous standard counselling session by means of a "checklist after standard counselling", which the genetic counsellor fills in immediately after each session. This checklist includes information about the participant's risks e.g. individual estimated risk of getting breast cancer, also describing the risks formats that were used during counselling. When risks are not yet known, because, for instance, medical records need to be checked, intervention takes place after a second visit. Thus, enforcement of an intervention implies that in the genetic counselling session with the genetic counsellor at least the woman's breast cancer risk group (e.g. low, moderate, high) was communicated.

After the intervention, all participants receive a BRISC brochure in which risks are presented corresponding to the format of the intervention given.

## Measures

### Outcome measures

Outcome measures are classified in four dimensions: 1) cognitive outcomes; 2) psychological well-being; 3) decision-making; 4) evaluation of the intervention (i.e. additional risk consultation). Table 3 shows which variables are measured in which questionnaires.

**Table 3 T3:** Outcome measures of the BRISC study in the different questionnaires

**Variables**	**Instruments**	**Questionnaires**				
		T0	T1	T1C	T2	T3/T2C

**Cognitive outcomes**						
Risk perception						
- numerical scales		X	X	X	X	X
- verbal scales		X	X	X	X	X
- graphical scales				X	X	X
Recall						X
Knowledge of familial breast cancer		X	X	X	X	X
**Psychological well-being**						
Cancer-related worries	CWS	X	X	X	X	X
Cancer-related distress and anxiety	IES			X	X	
Affect	PANAS	X	X	X	X	X
State anxiety	STAI-state	X	X	X	X	X
Anxiety and depression	HADS	X	X	X	X	X
**Decision-making**						
Intention		X	X	X	X	X
Behaviour		X				X
Informed choice	MMIC					
- attitudes towards DNA testing				X	X	
- genetic test-uptake				X	X	X
Decisional conflict	DCS			X	X	X
**Evaluation of the intervention**					X	X
**Personal characteristics**						
Sociodemographic characteristics		X				
Impact of family history				X	X	
Severity of breast cancer	IPQ-RAR			X	X	
Perceived Personal Control	PPC	X		X	X	X
Coping	UCL					X
General anxiety	STAI-trait			X	X	
Need for cognition	NCS			X	X	
Cognitive ability	CRT					X
Decision-making style	Melbourne DMQ					X
Social support	SEC			X	X	

#### Cognitive outcomes

*Risk perception *(primary outcome measure). Table 4 shows the risk perception measures used in the BRISC study. The graphical scales, i.e. Visual Analogue Scales (VAS scales) and graphical display, are only used as a measure after the intervention, to avoid participants of conditions 2 and 4 being triggered before the additional counselling session.

**Table 4 T4:** Risk perception as measured in the BRISC study

**Risk perception**	**Numerical scales**		**Verbal scales**	**Graphical scales**	
	X out of 100	%	Rating scale^a^	Graphical display^b^	VAS scale

**Population risk**					
Lifetime breast cancer risk in the general population	X	X	Very small – very large	X	X
**Risks among carriers**					
Lifetime breast cancer risk in carriers	X	X	Very small – very large	X	X
Risk passing a *BRCA1/BRCA2 *mutation to children	X	X	Very small – very large		
**Participant's risks**					
Perceived risk of having a hereditary predisposition to breast cancer	X	X	Very small – very large Easy to imagine – hard to imagine		
Perceived lifetime breast cancer risk	X	X	Very small – very large		
			Easy to imagine – hard to imagine		
			Very unlikely – very likely		
Perceived age-related breast cancer risk (next ten years)	X	X	Very small – very large Easy to imagine – hard to imagine		
			Very unlikely – very likely		
Appraisal of perceived breast cancer risk, independent of actual risk			Very small – very large Very unfearful – very fearful		
			Not worrisome at all – very worrisome		
Perceived breast cancer risk compared to the average Dutch Woman			Very strongly lowered – very strongly heightened		
**Risks among women with the same family history and age**					
Lifetime breast cancer risk in women with the same family history and age	X			X	X
Age-related breast cancer risk in women with the same family history and age (next ten years)	X			X	X

^a.^Rating scales from (1) – (7) except for: Very strongly lowered (1) – very strongly heightened (9).

^b.^Figure of 100 women.

*Recall *is assessed by asking women to what breast cancer risk group they belong: 1 (not increased risk group) to 5 (very strongly increased risk group). Two additional answering categories are "this has not been discussed" and "don't know (anymore)".

*Knowledge of familial breast cancer *is measured by using a 10-item questionnaire based on questionnaires designed by Lerman et al. [42] and Bluman et al. [43]; adapted and supplemented with items regarding breast cancer (age-related) risk. An expert panel ([name]) evaluated the questionnaire using a "true", "false" and "don't know" answering scale, and consensus was reached on the items used (Table 5).

**Table 5 T5:** Knowledge questions of familial breast cancer

	**Items**	True (T)/ False (F)
1	There is more than one gene that can increase the risk of breast cancer	*T*
2	With hereditary breast cancer, breast cancer develops generally more likely at a younger age compared to non-hereditary breast cancer	*T*
3	A father can pass down a genetic predisposition for breast cancer to his daughter	*T*
4	Even if a woman doesn't have a genetic predisposition for breast cancer, her children still can get the genetic predisposition from their grandmother (their mother's mother)	*F*
5	Regular breast cancer screening can prevent the development of breast cancer	*F*
6	A DNA test can determine whether one will or will not certainly develop breast cancer	*F*
7	Genetic inheritance is the main cause of breast cancer in most patients with breast cancer	*F*
8	All women who have a genetic predisposition for breast cancer will get cancer	*F*
9	With ageing, the residual risk of getting breast cancer becomes smaller	*T*
10	The risk of getting breast cancer within the next ten years is equal to the total lifetime risk of getting breast cancer	*F*

#### Psychological well-being

*Breast cancer-related worries *about the risk of developing cancer and the impact of worry on daily functioning is measured by an 8-item adapted Lerman Cancer Worry Scale (CWS) [44].

*Breast cancer-related distress and anxiety *is measured by a Dutch version of the 15-item Impact of Events Scale (IES) [45].

*Affect*, which can be subdivided into positive affect and negative affect (distress), is measured by the 20-item PANAS Scale (Positive and Negative Affect Schedule) [46]. Participants will be instructed to answer the questions in the context of "the past few days".

*State anxiety *is measured by a Dutch version of the 6-item version of the State scale of the Spielberger State-Trait Anxiety Inventory (STAI) [47].

*Anxiety and depression *is measured by a Dutch translation of the 14-item Hospital Anxiety and Depression Scale (HADS), using the timeframe of "last week" [48].

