### Intervention

The intervention consists of one additional consultation by a trained "risk counsellor" immediately after a standard genetic counselling session with a clinical geneticist, a clinical geneticist in training, or non-medical genetic counsellor, henceforth defined as a "genetic counsellor" (Figure 1). Since genetic counselling is seen as a psycho-educational endeavour with both educational and therapeutic elements [37], it is considered unethical to ask the genetic counsellors to present the intervention in a standardized and as objective a way as possible, thereby ignoring the specific needs of the patient. In addition, we assume that besides being unethical, it will not be feasible due to an additional workload for genetic counsellors.

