### Statistical analyses

Analyses will be performed to estimate the effect of the different interventions (formats) by comparing pre-test- (T0/T1) with post-test- (T2/T1C) outcome measures between the five different intervention groups and the control group, using multivariate analyses. At baseline (T0) and at T1 similar variables will be measured in order to be able to assess the effect of the regular counselling session with the genetic counsellor. Personal variables will be included as covariates. Repeated measures in MANOVA will be used to analyse changes over time and long-term effects (T3/T2C).

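### At T1, HADS and PANAS look back mostly to the time before the standard counselling session, so their T0–T1 change largely misses that session's effect

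*Protocol article*

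**What the plan says.** Four statements in the protocol article bear on this.

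- **Look-back periods** (Measures, Psychological well-being). HADS is answered "using the timeframe of 'last week". For PANAS, "Participants will be instructed to answer the questions in the context of 'the past few days". No separate instruction is given for T1.
- **Schedule** (Table 3). The HADS row reads "Anxiety and depression HADS X X X X X", so it is marked in every column: T0, T1, T1C, T2 and T3/T2C. The PANAS row has the same pattern.
- **Timing** (Procedure and Intervention). For T1, "A second questionnaire will be given after the standard genetic counselling session with the genetic counsellor and prior to the intervention". The added risk consultation takes place "immediately after a standard genetic counselling session", so T1 falls in a short gap. T2 in the intervention arms and T1C in the control arm come about two weeks later. Condition 6 has no questionnaire between the session and T1C.
- **Use** (Statistical analyses). At T0 and T1, "similar variables will be measured in order to be able to assess the effect of the regular counselling session". The same section takes T0/T1 as the pre-test and T2/T1C as the post-test when the five intervention groups and the control group are compared.

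**The concern.** A scale can show the effect of an event only if the period it asks about lies mainly after that event. At T1 the woman has just left the standard session, but HADS asks her about the past week and PANAS about the past few days. By instruction, both answers refer mainly to the run-up to the appointment.

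The T0–T1 comparison for these scales is then mostly a comparison of two pre-session periods. A flat result could be reported as counselling having no emotional effect, and a rise as counselling having caused distress. Either could simply reflect the days before the visit. For the same reason, T1 is not a post-session starting point for these two scales when the added consultation is assessed.

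**Working it through.** The plan states no figure here to reproduce. The check asks how much of each look-back period can lie after the session has begun, and then which planned comparisons depend on it.

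**1. Share of the look-back period after the session starts**

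Share = h / (24 × D), where h is the hours from session start to completion of T1 and D is the look-back in days.

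Inputs:
- HADS: D = 7, from the one-week instruction.
- PANAS: D = 2, 3 or 4. This is an assumption, because the protocol does not define a few days.
- h = 0.5 to 3. This is an assumption, because neither session length nor the delay to T1 is given.

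| Scale | D (days) | h = 0.5 | h = 3 |
|---|---|---|---|
| HADS | 7 | 0.5/168 = 0.3% | 3/168 = 1.8% |
| PANAS | 2 | 0.5/48 = 1.0% | 3/48 = 6.3% |
| PANAS | 3 | 0.5/72 = 0.7% | 3/72 = 4.2% |
| PANAS | 4 | 0.5/96 = 0.5% | 3/96 = 3.1% |

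About 98% or more of the HADS period and about 94% to 99% of the PANAS period therefore lie before the session.

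**2. The same periods at T2**

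T2 is 14 days after the intervention. The HADS period then begins 14 − 7 = 7 days after it. The PANAS period, taken as 4 days, begins 14 − 4 = 10 days after it. When the consultation directly follows the session, both periods lie wholly after both events.

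**3. Which comparisons are affected**

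Let s be the effect of the standard session on the scale, c_k the effect of the consultation in condition k, and λ (between 0 and 1) the fraction of s already visible in the T1 score. Suppose that s and any time trend are the same in all arms and that s persists to two weeks. Leaving the common trend out:

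- T0–T1 change, conditions 1–5: λs. This is the quantity the plan would read as s.
- T1–T2 change, condition k: (1 − λ)s + c_k.
- T1–T2 change, condition k minus condition j: c_k − c_j. Both s and λ cancel.
- T0–T1C change, condition 6: s.
- T0–T2 change in condition k minus T0–T1C change in condition 6: (s + c_k) − s = c_k. Again s and λ cancel.
- T1–T2 change in condition k minus T0–T1C change in condition 6: (1 − λ)s + c_k − s = c_k − λs.

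Only the first quantity fails because λ is small. The contrasts among formats do not depend on λ. With T0 as the pre-test, neither does the contrast with usual care. If T1 were used against condition 6, the mismatch would be λs, which shrinks as λ gets smaller.

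**The case against.** The strongest reply is that little of importance is touched. The planned analysis compares arms and does not rest on an uncontrolled change within one arm. None of the four research questions asks for the effect of standard counselling. The sentence that announces that assessment names no scale. HADS and PANAS are secondary, and the cancer worry scale and STAI-state are also at T0 and T1 with no look-back stated. All of this stands and limits the point to an ancillary analysis of two scales.

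A reader might infer that the intervention effect is also biased because the T1–T2 change takes in the session's effect. The documents do not support that. All of conditions 1–5 have the same session first, so it cancels between formats. Condition 6 has only T0 as a pre-test, and its T0–T1C change contains the session's effect too.

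A reader might also infer that T1 scores cannot contain any session effect, or that the percentages above are effect sizes. Neither follows. Current mood may colour a rating of the past week, and women need not weight every hour equally. The shares show what the instruction asks about. They do not estimate λ.

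Finally, where the risk is not yet known, the consultation follows a second visit. The protocol does not say when those women complete T1, so an earlier visit may fall inside or before the period rated. The session directly before T1 would still occupy little of it.

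**Conclusion.** The point holds in a limited form. For HADS and PANAS, the T0–T1 change mostly compares two pre-session periods and largely misses the effect of the standard session. T1 is not a true post-session pre-test for them. Two of the five well-being instruments are affected.

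Contrasts among conditions 1–5 are not biased by this, and risk perception, the primary outcome, is unaffected. T1 scores on the two scales remain valid as descriptions of the pre-session period.

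The conclusion rests on the stated look-back instructions applying at T1 as at the other time points, and on T1 being completed within hours of the session. It holds across the assumed 0.5 to 3 hours and two to four days. The cancellation across arms assumes a session effect and time trend common to the arms. How much of a session effect would show at T1 through current mood cannot be derived from the documents.

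**What to change.** In the Statistical analyses section:

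- Exclude HADS and PANAS from the T0–T1 assessment of the standard session. Base it on measures for which the Measures section states no past-period window, such as STAI-state.
- Name T0 as the pre-test for HADS and PANAS in all six arms: T0–T2 in conditions 1–5 against T0–T1C in condition 6.
- Label any T1 values of these scales as pre-session scores, to be used only as a covariate in comparisons among conditions 1–5.

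Optionally, drop both scales from T1. That removes 14 + 20 = 34 items while women wait between two consultations, but also gives up the covariate.

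Do not give PANAS a current-moment instruction at T1 alone, because T1 would then no longer be comparable with T0 or T2.

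The cost is a few sentences of analysis text. The downside is that these two scales yield no estimate of the standard session's effect.
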